#### Ergospirometry

All patients will perform a maximal cardiopulmonary exercise test on a cycle ergometer [50]. All the exercise tests will be performed at the same time of day (between 8.30 and 11.30 am). The test will be performed at 4 weeks after surgery (t_1_), 9 weeks after surgery (t_3_) and at 12 weeks after surgery (t_4_).

During the exercise test, an electronically braked e-Bike (Acertys) is used. The cycling frequency is set at 70 cycles/min. In addition, exercise tests will be prematurely ended when myocardial ischemia and/or severe ventricular arrhythmias would occur and the subject will be excluded from the study. Both the starting and incremental cycling resistance will be set between 10 and 40 W and increased every minute to volitional fatigue.

Pulmonary gas exchange analysis will be performed by using cardiopulmonary ergospirometry device (Jaeger MasterScreen CPX). Before every test, a gas and volume calibration will be executed. During the test, environmental temperature is kept stable (19–21 °C). Oxygen uptake, expiratory volume and respiratory exchange ratio are collected breath-by-breath and averaged every 10 s. Using a 12-lead ECG device, heart rate is monitored and averaged every 10 s. In addition, maximal cycling resistance and total test duration are reported. By V-slope method, ventilatory threshold is calculated. The criteria for defining a maximal cardiopulmonary exercise test are an achieved heart rate > 85% of the maximal predicted heart rate, and/or a Respiratory gas Exchange Ratio (RER) > 1,09 [51].

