### Participants

Subjects admitted to the hospital for elective CABG with median sternotomy will be eligible for this study. Participant recruitment began in January 2010 and is expected to finish in December 2017. Subjects with diagnosed chronic obstructive pulmonary disease, diagnosed neurologic disease that prevents participation in the cardiac rehabilitation programme, diagnosed nephrological disease that requires haemodialysis, prior thoracic surgery, surgery in the epigastric, right or left hypochondriac region will be excluded. Subjects will also be excluded if the subject has a prolonged stay (>5 days) in the intensive care unit. All CABG surgery procedures will be performed by the same surgical team. Subjects may not receive any other manual treatment on the spine and/or thorax during the study.

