**Fig. 2 Fig2:**
[figure not shown]
Study content for the schedule of enrolment, interventions, and assessments. -t_2_: preoperative, -t_1_: 9^th^ postoperative day, t_0_: start of cardiac rehabilitation programme (3 weeks postoperative), t_1_: 4 weeks postoperative, t_2_: 5 weeks postoperative, t_3_: 9 weeks postoperative, t_4_: 12 weeks postoperative, t_5_: 12 months postoperative. SVC: slow vital capacity. VAS: visual analogue scale. MacNew QLQ: MacNew quality of life questionnaire

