#### Osteopathic procedure

The protocol used for OT and osteopathic examination (OE) incorporates a number of osteopathic techniques and will be performed by five registered osteopaths with a minimum experience of 5 years. The protocol used is based on the work of Dickey [31] and supplemented with the findings of other authors [32–35]. The most common findings found in literature are:Decrease in costal mobility [8, 10, 11, 36]Decrease in pulmonary function [6, 8, 10]Decreased thoracic mobility [8, 10, 11, 31]Dysfunction of the abdominal diaphragm [31, 37–41]

The nomenclature, indications and contraindications for the OE and OT are based on the work of Nicholas and Nicholas [32], Chila [42], on the professional competence profile of an osteopath [43–45] and the benchmarks of the World Health Organisation [46].

The OE protocol is a set of standardised test for a first evaluation of the patient. The findings are noted on a predefined Microsoft excel-file by the Osteopath.Inspection: in standing, seated and supine: observe the patient in posterior, anterior and lateral view to develop the most complete understanding of the patients makeup before performing the remainder of the OE ([32] p. 3–14).Position test of the thoracic spine (seated) ([42] p.561)Intersegmental motion testing:thoracic seated ([32] p. 42–49)cervical supine ([32] p. 60–65)costal supine ([32] p. 52–59
Costal motion testing supine [32] (p.53–56)Evaluation of the abdominal diaphragm (seated and supine) ([42] p. 567)

The OT consists of a standardised treatment protocol (Table 1) and a supplementary treatment protocol of the dysfunctions found during the examination. In order to be reproducible, the different treatment possibilities are discussed and presented (Fig. 3). The OT will take 30–45 min. The examination room is air-conditioned and has a constant temperature of 21–22 °C. The OT will be performed at 4 weeks postoperative (t_1_), 5 weeks postoperative (t_2_), 9 weeks postoperative (t_3_) and at 12 weeks postoperative (t_4_). OT can be considered as safe, and major adverse events are very rare [47, 48]. In case adverse events should occur, they will be recorded and discussed in the final paper.

**Table 1 Tab1:** Standard treatment protocol OstinCaRe study

Osteopathic technique	Description	Rationale for use

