#### MacNew quality of life questionnaire (QLQ) and Visual analogue scale (VAS)

The Flemish version of the MacNew QLQ and the VAS for pain and thoracic stiffness are delivered to the patients by a blinded person of the cardiac rehabilitation centre at enrolment (t_0_), 12 weeks after surgery (t_4_) and at 12 months after surgery (t_5_). The Flemish version of the MacNew QLQ demonstrates good psychometric properties and is recommended as a specific instrument for assessing and evaluate health-related quality of life in Flemish-speaking patients [52].

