### Statistical analysis

Data will be analysed by a statistician blinded to group allocations, using the Statistical Package for the Social Sciences (SPSS) v. 22.0 (IBM). First, descriptive statistics will be executed, with calculation of means and standard deviations, and analysis of data distribution (by Shapiro-Wilk test) and evaluation of outliers. In case of normal data distribution, one-way ANOVA with repeated measures will be executed to analyse and compare changes in parameters between groups (with Bonferroni corrections for multiple comparisons). Relations between parameters will be examined by Pearson correlations. In case of non-normal data distribution, absolute changes in parameters will be compared between groups by Mann Whitney U-tests (with Bonferroni corrections for multiple comparisons). Relations between parameters will be examined by Spearman correlations. Statistical significance is set at *p* < 0.05, two-tailed. Observed statistical power will be calculated by use of GPower v. 3.1. Intention to treat analysis will be executed. Missing data will be handled using the last observation carried forward imputation technique. Dropouts and withdrawals from the study will be recorded through the intervention and follow-up periods. When differences in baseline phenotype are present, these differences will be taken into account during analysis of treatment effect between groups, by regarding them as co-variates.

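### Excluding patients from the study for ischaemia or arrhythmia at a post-treatment exercise test is not reconciled with the intention-to-treat analysis

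*Protocol article*

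**What the plan says.** Protocol article, Ergospirometry: "exercise tests will be prematurely ended when myocardial ischemia and/or severe ventricular arrhythmias would occur and the subject will be excluded from the study". The sentence is not limited to the first test or to the VO2max data. The same section gives the schedule: "The test will be performed at 4 weeks after surgery (t_1_), 9 weeks after surgery (t_3_) and at 12 weeks after surgery (t_4").

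The timing of treatment comes from two other places. The legend of Fig. 2 gives "t_0_: start of cardiac rehabilitation programme (3 weeks postoperative"), and Osteopathic procedure states "The OT will be performed at 4 weeks postoperative (t_1_), 5 weeks postoperative (t_2"), followed by two later sessions. The questionnaire section lists the MacNew and VAS assessments "at enrolment (t_0_), 12 weeks after surgery (t_4_) and at 12 months after surgery (t_5"), which places enrolment at week 3.

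Statistical analysis states "Intention to treat analysis will be executed" and "Missing data will be handled using the last observation carried forward imputation technique". It adds that dropouts and withdrawals will be recorded. It does not mention patients excluded at an exercise test. Nothing in the article says whether they stay in the analysis set or are still measured at weeks 12 and 52.

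**The concern.** Intention to treat requires that every randomised patient is followed and analysed in the allocated group, whatever happens later. A rule that takes patients out of the study for something that occurs after allocation works against this. If the chance of the event, or the kind of patient who has it, differs between arms, the groups that remain are no longer the groups that were randomised.

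The protocol's own rationale does not allow such a difference to be ruled out. Table 1 credits one standard technique with an effect on parasympathetic function, and the Discussion cites immediate haemodynamic effects of osteopathic treatment after CABG.

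The loss is also unnecessary. The primary outcome, change in SVC at 12 weeks, comes from a separate spirometry test and does not depend on completing an exercise test. The same is true of the VAS and MacNew outcomes.

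**Working it through.** **1. Do the exclusions fall after randomised treatment has begun?**

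| Exercise test | Osteopathic sessions before it | After the start of randomised treatment? |
|---|---|---|
| Week 4 (t1) | First session is also at t1; order not given | Possibly |
| Week 9 (t3) | Weeks 4 and 5 at least | Yes |
| Week 12 (t4) | Weeks 4 and 5 and the t3 session; the fourth session is at t4 | Yes |

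The label t3 is week 9 in Fig. 2, Ergospirometry and Osteopathic procedure, but week 8 in Spirometry; the Abstract also puts the third session at week 8. Those passages need reconciling, but under either label t3 follows the first two sessions.

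**2. What happens under each reading?**

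*Plain reading: the patient leaves the study and the analysis.* The analysis set then depends on a post-randomisation event and is not the intention-to-treat set.

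*Lenient reading: the patient is a withdrawal, kept in the analysis by last observation carried forward.* The measurement schedules give the following.

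| Event at | SVC | VAS and MacNew |
|---|---|---|
| Week 9 test | The t3 value at best stands in for weeks 12 and 52 | The only earlier value listed is t0, so change from t0 is imputed as zero at weeks 12 and 52 |
| Week 12 test | Week 12 value if already taken, otherwise t3; week 52 is imputed | Week 12 value if already taken, otherwise t0; week 52 is imputed |

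On direction, the Background gives a fall in vital capacity of 30–60% in the first week, and Sample size assumes a 12% fall in IVC at week 12. Capacity therefore recovers in between, and an earlier value tends to understate the week 12 value. The level at t3 is not given, so the error cannot be sized. From week 12 to week 52 the article's figures (12% at both times) suggest little average change. The loss there is of information, with no known direction.

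**3. How many patients?** The plan states no figure for this. With 2 × 154 = 308 patients and an assumed 1–5% affected:

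- 308 × 0.01 = 3.08, about 3
- 308 × 0.05 = 15.4, about 15

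**4. Effect on power.** Inputs are the plan's effect size of 0.50, two-sided alpha of 0.05, 154 per group and 20% dropout, using a two-sample t-test.

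| Assumed exclusion | Left per arm | Power |
|---|---|---|
| 0% | 154 × 0.80 = 123.2 | 97.4% |
| 1% | 154 × 0.79 = 121.7 | 97.3% |
| 5% | 154 × 0.75 = 115.5 | 96.6% |

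Power is this high because the stated inputs need only 64 per group, against the planned 128 before dropout. That is a separate matter. At the smaller effect of about 0.35 that 128 per group would detect with 80% power, the figures are 78.4%, 77.9% and 75.8%.

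**5. Effect on bias (plain reading).** If excluded patients differ from those remaining by D standard deviations, and a fraction e of an arm is excluded, the mean of the remaining patients is shifted by e × D. The bias in the group difference is then (e_B − e_A) × D, with e and D assumed:

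- 2% against 5%, D = 0.5: 0.03 × 0.5 = 0.015 SD
- 2% against 5%, D = 1.0: 0.03 × 1.0 = 0.03 SD
- 5% against 10%, D = 1.0: 0.05 × 1.0 = 0.05 SD
- equal rates and equal D: 0

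The planned effect is 0.50 SD.

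**The case against.** The best defence is that leaving the study is not the same as leaving the analysis. The article announces intention to treat, names an imputation method and says withdrawals will be recorded. Taken together, an excluded patient could be a safety withdrawal analysed as randomised. This stands in part: a reader might infer that SVC, pain and quality-of-life data already collected are deleted, and the text does not say so. It does not say the opposite either, and step 2 shows that this reading still discards values that could be measured.

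Other stronger readings are tempting, and the document does not support them:

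- **That all three tests follow the start of osteopathic treatment.** The order of the week 4 test and the first session is not given, and the text does not date randomisation. An exclusion at week 4 may precede any osteopathic treatment.
- **That patients are excluded on an outcome.** Ischaemia and arrhythmia are not listed as outcomes. The trigger is a safety event seen while an outcome is measured.
- **That the intensive-care criterion, "Subjects will also be excluded if the subject has a prolonged stay (>5 days) in the intensive care unit", is a second post-randomisation exclusion.** It is listed with the eligibility criteria, and enrolment is placed at week 3, when such a stay would ordinarily be known. A preoperative SVC shows a measurement, not an allocation.
- **That dozens of patients would be lost.** A 5% rate at each of three independent tests gives 308 × (1 − 0.95³) = 44. The rate is assumed, and independence is implausible because those who remain have already passed a maximal test.

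Blinded outcome assessors limit selective exclusion, but not a real difference in events between arms.

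**Conclusion.** The point holds. For the week 9 and week 12 tests, and possibly the week 4 test, the article fixes a post-randomisation exclusion and does not reconcile it with its intention-to-treat analysis. Neither reading is satisfactory: one drops randomised patients for an event that treatment could influence, and the other replaces obtainable values with older ones.

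The numerical effect is probably small. On an assumed 1–5% of patients, about 3 to 15 of 308 are affected, and power at the planned effect stays above 96%. Under the assumed differences between arms the bias is about 0.015 to 0.05 SD, and it is zero if rates and patient types are alike. The document gives no event rate, so these figures are illustrations. What is at stake is whether the analysis is the one announced, more than power. The change should be made because it is cheap, not because the trial's result is likely to turn on it.

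**What to change.** Reconcile Ergospirometry with Statistical analysis by replacing the exclusion clause with wording such as:

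*When an exercise test is ended early for these reasons, VO2max for that visit is recorded as not obtained. Where consent and clinical condition allow, the patient remains in study follow-up for SVC, VAS and MacNew at the scheduled visits. The patient is analysed in the randomised group.*

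The criteria for ending a test, and decisions on the patient's care and treatment, are untouched and stay with those responsible for them.

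The cost is a short text change. No visits or measurements are added, because SVC, VAS and MacNew are already scheduled at weeks 12 and 52. Since recruitment is under way, any patients already excluded under this rule should be counted by group and reported, and included in the analysis as randomised with the data available.

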#### MacNew quality of life questionnaire (QLQ) and Visual analogue scale (VAS)

The Flemish version of the MacNew QLQ and the VAS for pain and thoracic stiffness are delivered to the patients by a blinded person of the cardiac rehabilitation centre at enrolment (t_0_), 12 weeks after surgery (t_4_) and at 12 months after surgery (t_5_). The Flemish version of the MacNew QLQ demonstrates good psychometric properties and is recommended as a specific instrument for assessing and evaluate health-related quality of life in Flemish-speaking patients [52].

### Data management

All procedures comply with confidentiality standards for medical data. Authorized medical staff treating the patient is granted unconstrained access to the patients’ data, whereas restricted access to anonymized data is granted to other local staff and researchers. All data will be entered electronically and all original forms will be kept at the study site. Participant files are stored in alphabetical order and stored in a secure and accessible place and manner at the study site. Participant files will be maintained in storage for a period of 3 years after completion of the study. During this time, access to the completely encrypted dataset can be obtained on individual demand. A back-up of all data will be performed every week on a USB-stick and on the hospitals’ backup server. Because the known minimal risk of this study a data monitoring committee is not needed [53]. Important protocol modifications during this study will be communicated to the trial registry and the journal of publication.

### Sample size

A priori sample size calculation is based on pulmonary function (by GPower 3.1). The hypothesis for the OstinCaRe study is that the addition of OT towards endurance exercise training increases inspiratory vital capacity (IVC) by 12% during the follow-up of CABG patients. Power analysis is based on a 12% decrease in IVC at 12 weeks after surgery [11]. As a result, an increase of approximately 12% of the IVC is expected at 12 weeks after CABG. Sample size is computed considering an effect size of 0.50, a statistical power of 0.80 and an alpha level of 0.05. The power analysis outcome defines that 128 subjects per group are needed. Based on unpublished data of the cardiac rehabilitation centre a dropout rate of 20% is to be expected. Therefore, 154 subjects per group are needed. Participant recruitment began in January 2010 and is expected to finish in December 2017. Interim analysis is planned when 154 (50%) patients are included. The study can be stopped before reaching sample size if there is a significant change in surgery technique, which could compromise reproducibility and comparability throughout the study. The author makes the final decision to terminate the trial.

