### Outcome measures

Primary outcome measure will be the mean difference in change from baseline in SVC at 12 weeks after surgery between the two groups.

Secondary outcome measures will include:Change from baseline in SVC at 52 weeksChange from baseline in MacNew QLQ at 12 and 52 weeks after surgeryChange in pain from baseline on Visual Analogue Scale (VAS) at 12 and 52 weeks after surgeryChange in thoracic stiffness from baseline on VAS at 12 and 52 weeks after surgeryChange from baseline in maximal aerobic capacity (VO2max) at 12 weeks after surgery

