#### Spirometry

The Pocket-Spiro USB100 (Medical Electronic Construction & Logistic nv, Belgium) will be used for measuring pulmonary function. All patients are asked to perform a slow vital capacity (SVC) test, consisting of three measurements. For VC the best of the three measurements is used and for IVC the average of three measurements is used [49]. The instrument is calibrated prior to the test. When an OT is planned, SVC will be measured at least 2 days after OT, because the study wants to measure long-term effects (effects of the entire intervention), instead of any short-term effect (within the first hours after OT). SVC will be measured preoperative (-t_2_), 9^th^ postoperative day (-t_1_), 4 weeks after surgery (t_1_), 8 weeks after surgery (t_3_), 12 weeks after surgery (t_4_) and at 12 months after surgery (t_5_).

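### The 128 per group is the total for the stated inputs (64 per group), and 154 does not preserve 128 after 20% dropout, so the stated size and power do not fit together

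*Protocol article*

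**What the plan says.** The Sample size section gives its inputs in one sentence: "Sample size is computed considering an effect size of 0.50, a statistical power of 0.80 and an alpha level of 0.05". It then states the result: "The power analysis outcome defines that 128 subjects per group are needed". It expects 20% dropout and ends with: "Therefore, 154 subjects per group are needed". The Abstract repeats the figure as 308 patients, 154 in each arm, and the Sample size section places the interim analysis at 154 patients, described as 50%.

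The other inputs come from elsewhere in the article. Randomisation and masking sets 1:1 allocation. The Statistical analysis section makes testing two-sided: "Statistical significance is set at *p* < 0.05, two-tailed". Outcome measures defines the comparison: "Primary outcome measure will be the mean difference in change from baseline in SVC at 12 weeks after surgery between the two groups".

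The calculation is written for inspiratory vital capacity (IVC). The Spirometry section describes one SVC test with two scoring rules: "For VC the best of the three measurements is used and for IVC the average of three measurements is used".

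**The concern.** The combination of d = 0.50, 80% power and two-sided alpha 0.05 is a familiar one, and 128 is its well-known total for two groups. Seeing 128 attached to each group suggests that the software's total was read as a group size. The same figure recurs as 154 per arm, 308 overall and 154 at the halfway point, so it sets the size of the trial and is not a slip of wording.

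Three things are at stake:

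- Readers will judge the result against a design said to have 80% power at d = 0.50, which is not its real property. An effect well below 0.50 could reach significance in a trial described as sized for 0.50.
- Patients and recruitment time are committed to a number that the stated assumptions do not support. The interim at 154 patients (77 per arm) is already close to the whole trial that those assumptions require.
- The calculation cannot be tied to the primary outcome until the article says which reading of the SVC test is primary.

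**Working it through.** **Inputs.** Effect size 0.50, power 0.80, alpha 0.05 and dropout 20% (Sample size); two-sided testing (Statistical analysis); 1:1 allocation (Randomisation and masking); between-group difference in mean change (Outcome measures). The article does not name the effect-size measure, so 0.50 is taken as Cohen's d.

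**Step 1: size from the stated inputs.**

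- Normal approximation: n per group = 2(z₀.₉₇₅ + z₀.₈₀)²/d² = 2(1.960 + 0.842)²/0.25 ≈ 62.8, so 63.
- Noncentral t: 63.8, so **64 per group, 128 in total** (power 0.801).
- Two-group ANOVA with f = d/2 = 0.25: 127.5, so 128 in total.

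The plan's 128 is reproduced exactly, but only as the total.

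**Step 2: does any other reading give 128 per group?**

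| Variant (0.50, power 0.80 unless stated) | Result |
|---|---|
| One-sided t-test | 51 per group |
| Mann-Whitney, efficiency 3/π to 0.864 | 67 to 74 per group |
| Two-group ANOVA, f = 0.50 | 34 in total |
| Repeated-measures ANOVA, between groups, f = 0.25, 2 to 6 measurements, correlation 0.5 assumed | 98 down to 76 in total |
| Same, group-by-time interaction | 34 down to 20 in total |
| t-test, alpha 0.01 | 96 per group |
| t-test, alpha 0.001 | 140 per group |
| t-test, alpha 0.05, power 0.975 / 0.98 | 124 / 130 per group |

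None gives 128 per group at power 0.80 and alpha 0.05. That figure needs power of about 0.98, or an alpha between 0.001 and 0.01.

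**Step 3: dropout.**

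- The plan's route: 128 × 1.2 = 153.6, so 154.
- Retaining 128 after 20% loss: 128/(1 − 0.20) = **160 per group**.
- What 154 leaves: 154 × 0.80 = 123.2, so **123 per group**.
- Dropout that 154 covers: 1 − 128/154 = 16.9%.
- From the correct starting point: 64/0.80 = **80 per group, 160 in total**.

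**Step 4: what the planned size delivers** (two-sided t-test, alpha 0.05).

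| Analysed per group | Power at d = 0.50 | d with 80% power |
|---|---|---|
| 64 | 0.801 | 0.50 |
| 123 (154 less 20%) | 0.974 | 0.359 |
| 128 (as claimed) | 0.979 | 0.352 |
| 154 (all randomised) | 0.992 | 0.320 |

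At the interim, 77 per group would have power 0.869 at d = 0.50 if all were analysed.

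**Step 5: excess.** 308 − 160 = 148 patients. January 2010 to December 2017 is 96 months, and 308/96 ≈ 3.2 a month. At that average pace 148 patients take about 46 months.

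**Step 6: powered variable against primary variable.** The calculation concerns IVC, which is scored as the mean of three measurements. The primary outcome is SVC. The SVC test yields both VC (best of three) and IVC, and the article does not say which of them is the SVC of the primary outcome.

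**The case against.** The strongest reply concerns direction. The error makes the trial larger than its inputs require. Detection of the stated effect is not endangered, the type I error is untouched, and 80% power is exceeded. This is correct, and the finding should be read as over-sizing. It does not make the paragraph true, because the stated effect size, power, group size and dropout allowance cannot all hold together.

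Second, 123 per group is a completers' count. The Statistical analysis section specifies intention to treat with last observation carried forward, so up to 154 per group could enter the analysis. That stands. Power at d = 0.50 is better given as 0.974 to 0.992, with the caveat that carried-forward values may not carry full information.

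Third, the dropout slip is small by itself: six per group, and power of 0.974 against 0.979. That also stands. It matters only because the figure of 154 is presented as following from 128 and 20%.

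Fourth, IVC is one reading of the SVC test, and a standardised effect of 0.50 gives the same n under either label. So the fair statement is that the article does not specify which reading is primary. It does not prove that they differ.

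Fifth, the 46 months assume even accrual over an expected recruitment window, and the article gives no accrual data. It is an illustration only.

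**Conclusion.** The concern holds. On the plan's own inputs the requirement is 64 analysed per group, or 80 randomised per group with 20% dropout (160 in all). The plan states 128 and 154 per group and enrols 308, close to double. The dropout step is also wrong on its own terms, since 128 retained would need 160 randomised per group. The real property of 308 patients is 97% to 99% power at d = 0.50, or 80% power at d = 0.36 with 123 per group (d = 0.32 with 154).

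The conclusion assumes that 0.50 is Cohen's d for a two-group comparison. The article names no test for the calculation and gives no standard deviation linking the 12% change in IVC to 0.50, but the other readings tried do not give 128 per group either. That a software total was misread is an inference from the exact match. The arithmetic does not depend on it.

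The paragraph has to be corrected because the trial's headline size rests on it.

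**What to change.** Rewrite the Sample size paragraph in one of two ways:

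- **Correct the size.** State that d = 0.50, power 0.80 and two-sided alpha 0.05 need 64 per group (128 in total), and 80 per group (160 in total) allowing for 20% dropout. The Abstract and the 50% interim point would then have to follow, the latter at 80 patients.
- **Keep 308 and state what it delivers.** With 20% loss, 123 completers per group remain, giving 97% power at d = 0.50 or 80% power at d = 0.36. If all 154 per group are analysed under the carried-forward rule, the figures are 99% and d = 0.32. Say which count the statement refers to, so that it agrees with the Statistical analysis section.

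In either case, name the effect-size measure and the test, compute dropout as n/(1 − dropout), and name one spirometric variable (VC as best of three, or IVC as mean of three) as the primary SVC variable, with the calculation stated for it.

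The cost is the rewording of one paragraph, plus matching edits elsewhere if the size is changed. No patients are added. If 308 is kept, the stated power becomes more favourable and the number of completers falls from the claimed 128 to 123 per group.
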